### Development of the risk and difficulty stratification index

3.6

Following the consensus phase, the next step is to develop the formula for the risk prediction index. In this phase, the weights assigned by both surgeons and anaesthetists (ie, the median reference value) will be incorporated into a formula, which will then be normalised to a value ranging from 0 to 100. Similar to the Comprehensive Complication Index (CCI) formula [23,24], variables may be included to ensure that the model assigns higher values for multiple and severe complications while yielding lower values for single and minor peri- and postoperative complications. This approach will enhance the precision of differentiating between the severity and impact of pre- and postoperative risk factors. Organ-specific scoring systems will be developed following the same methodology.

Based on the outcomes of the Delphi process, we will determine whether a single formula or index is sufficient to address all three objectives outlined or whether multiple indices are required. Specifically, one index may be necessary to assess preoperative factors alone (eg, to enhance decision-making, optimise the allocation of critical care resources, or designate surgeries as teaching cases), while another index may be needed to incorporate both pre- and intraoperative factors for broader objectives. If surgical difficulty requires an independent calculation, a third distinct index may be warranted.

As highlighted previously, a surgeon’s learning curve—defined by a cumulative case volume—is a critical factor. This curve will be stratified into experience-based stages: 0–20 cases, 21–50 cases, 51–100 cases, 101–250 cases, 251–500 cases, and >500 cases. Proficiency typically plateaus after approximately 500 cases.

The assertion that surgical proficiency plateaus after around 500 cases is supported by studies analysing learning curves in complex surgical procedures. Research using a cumulative sum (CUSUM) analysis and other models has demonstrated that significant improvements in performance metrics—such as operative time, complication rates, and technical outcomes—tend to stabilise after approximately 500 cases, particularly in highly complex surgeries [25,26].

This stratification serves two purposes: (1) it allows the estimation of how increasing surgical experience reduces case difficulty and risk, and (2) it helps determine whether a procedure is suitable for a teaching setting.

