For inclusion in the initial patient cohort (cohort 1), all patients who underwent open or minimally invasive RC and urinary diversion between 2000 and 2021 were selected. Cohort 2 includes all patients who underwent open or minimally invasive RP between 2000 and 2020. Cohort 3 comprises all patients who underwent PN, RN, RNU, and RPLND. All variables from the CAMUS database have been included in the analysis.

Certain variables were adjusted for analytical purposes, such as categorising renal function into grades 1–5 and grouping intervention events (eg, intensive care treatment) into broader categories with subgroups (eg, cardiac and pulmonary intensive care). These adjustments were made to establish preoperative comorbidity categories and transform non-normally distributed variables. The primary study outcomes are the CDC/CAMUS grade or death within 90 d and the Comprehensive Complication Index (CCI).

Preoperative (expected/known) risk and difficulty factors used to calculate patient-specific risks and surgical difficulty were selected a priori based on their predictive value, routine availability to the surgeon before the operation, and clinical face validity. Similarly, intraoperative (unexpected/unknown) risk and difficulty factors were selected based on their predictive value, the surgeon’s expertise, and clinical validity. Immediate postoperative factors that refine risk estimation follow the same methodology.

All preoperative, intraoperative, and immediate postoperative factors will be evaluated using the Delphi method, as described previously.

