Logistic regression will be used to examine the relationship between major complications/death, and the risk index score (treated as an ordered categorical variable based on predefined categories) and its components across the three patient cohorts. Model discrimination will be assessed by calculating c-statistics (area under the receiver operating characteristic curve). For model calibration, the Hosmer-Lemeshow (HL) goodness-of-fit test will be used to compare predicted versus observed outcomes between the two cystectomy cohorts. In the final cohort, differences in complication rates across individual scores will be compared using chi-square tests. Additionally, using morbidity (complicated/uncomplicated) and mortality (dead/alive) as dichotomous dependent variables, multiple logistic regression models will be derived. Overall model significance will be assessed via the model chi-square statistic, and differences between observed and expected outcomes will be evaluated using the HL test.

To develop the surgical difficulty index, pre-, intra-, and postoperative parameters and outcome measures will be determined by experienced high-volume surgeons (≥1000 major interventions and >10 yr of surgical experience) using the Delphi method. Pre- and perioperative parameters that potentially increase operative difficulty and risk will be assessed using a 5-point scale, as shown in Supplementary Tables 1–3. Primary outcome measures for surgical difficulty will include operation duration, blood loss and transfusion, use of haemostatic agents, and the surgeon’s judgement (on a scale from 0 to 100).

The performance of the universal surgical risk calculator, which includes multiple specialities and hundreds of procedures, will be compared with the performance of our risk calculators, specifically programmed for this score development. This comparison will be made for individual procedures (eg, RC and RP).

Alternatively, to create risk prediction models, random-intercept, fixed-slope hierarchical models (using SAS GLIMMIX) will be employed. These models account for case clustering within hospitals and impose an empirical Bayes-type shrinkage adjustment. As a result, both universal and procedure-specific surgical risk calculators will be developed. The performance of the universal versus procedure-specific models will be evaluated using three metrics: the c-statistic, the HL statistic (in a revised graphical form), and the Brier score.

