Prediction models for mortality, CCI, blood loss, operating time, and other outcomes will be developed using logistic regression with stepwise selection based on the AIC. Cumulative C-indices will be recorded at each step of model development.

Given the HL test’s sensitivity to sample size, graphs will be constructed based on sequential groups with equal observed events rather than equal patient numbers (thus, low-risk groups will have more patients than high-risk groups).

For evaluating risk prediction accuracy and comparing the universal and procedure-specific surgical risk calculators, the Brier score will be considered the most appropriate measure of model performance. Results from 2 yr of data used for model development will be compared with those from the 3rd year of data used for validation.

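### Section 4.1 assigns logistic regression to the Comprehensive Complication Index, blood loss and operating time, which are not binary, and gives no threshold or other model for them

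*Protocol article*

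**What the plan says.** Section 3.7 (Data collection) sets the primary outcomes: "The primary study outcomes are the CDC/CAMUS grade or death within 90 d and the Comprehensive Complication Index (CCI"). For surgical difficulty, section 4.1 adds: "Primary outcome measures for surgical difficulty will include operation duration, blood loss and transfusion, use of haemostatic agents, and the surgeon’s judgement". Table 2 lists estimated blood loss in ml and duration of operation in min.

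Section 4.1 then fixes one method for several outcomes together: "Prediction models for mortality, CCI, blood loss, operating time, and other outcomes will be developed using logistic regression", with stepwise selection by AIC. C-indices are to be recorded at each step of model building. The same section uses the area under the ROC curve for discrimination, Hosmer-Lemeshow graphs for calibration, and the Brier score as the preferred measure for comparing universal with procedure-specific calculators. Sections 4.2 and 4.3 repeat the C-index, Hosmer-Lemeshow and Brier measures.

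The outcomes that section 4.1 explicitly makes binary are morbidity and mortality: "using morbidity (complicated/uncomplicated) and mortality (dead/alive) as dichotomous dependent variables". Elsewhere it uses major complications or death as the event.

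**The concern.** Plain logistic regression models the probability of an event. CCI, blood loss and operating time have no event until someone defines one, and the article does not. An analyst who follows the sentence must choose a split for each outcome. The cohorts already exist (section 3.7: cystectomy 2000 to 2021, prostatectomy 2000 to 2020), so a cut-off not fixed in advance could be chosen with the data in hand.

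Two things are at stake. First, every patient on the same side of a cut is treated as having the same outcome, so the models lose information on the scale the outcome was chosen for. Second, a freely chosen cut-off can flatter the reported discrimination. The problem reaches primary outcomes on both the risk side (CCI) and the difficulty side (blood loss, operating time). On the difficulty side, section 2.2 wants a metric for comparing surgeons and procedures.

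**Working it through.** The plan states no figure on this point, so there is none to reproduce. The check is mainly one of text.

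**Outcome scale against assigned model**

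| Outcome | Scale in the article | Status | Threshold given as an outcome | Model assigned |
|---|---|---|---|---|
| Mortality | dead/alive (4.1) | part of a primary outcome (3.7) | not needed | logistic: fits |
| CCI | graded index (3.6) | primary (3.7) | none | logistic: does not fit as written |
| Blood loss | ml (Table 2) | primary for difficulty (4.1) | none | logistic: does not fit as written |
| Operating time | min (Table 2) | primary for difficulty (4.1) | none | logistic: does not fit as written |

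The abbreviation CCI also stands for the Charlson Comorbidity Index in the Introduction. That is a baseline measure, so as an outcome in section 4.1 CCI can only sensibly mean the Comprehensive Complication Index. Section 3.6 cites that index's formula as a pattern for giving more weight to multiple and severe complications than to single, minor ones, so it is graded.

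**Does the text supply what is missing?**

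1. The 120 and 180 min bands in section 4.1 are point levels for operation duration as a component of the score, that is, as a predictor.
2. The 100 to 500 ml band in section 3.4 grades blood loss as a risk parameter, again as a predictor.
3. The ordered categorical variable in section 4.1 is the risk score as a predictor. No ordinal outcome model is named.
4. The hierarchical alternative in section 4.1 (GLIMMIX) could take other distributions, but none is given, and it is judged by the c-statistic, Hosmer-Lemeshow and Brier score.
5. The Hosmer-Lemeshow graphs are built from groups with equal numbers of events, which presupposes a binary outcome.

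**Illustration of the information lost by a split**

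Assume a normally distributed outcome and a small effect. Let q be the share of patients above the cut, c the corresponding normal quantile and φ the standard normal density. The efficiency of the binary outcome relative to the continuous one is φ(c)² / [q(1 − q)]. The protocol gives no cut, so q is assumed over a range.

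| q | Efficiency | Patients needed for equal information (1/efficiency) |
|---|---|---|
| 50% | 2/π = 0.64 | 1.57 times |
| 25% | 0.54 | 1.86 times |
| 20% | 0.49 | 2.04 times |
| 10% | 0.34 | 2.92 times |

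At the median, φ(0)² = 1/(2π), and dividing by 0.25 gives 2/π = 0.637, a loss of about 36%. At q = 10% the loss is about 66%.

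**The case against.** The best defence is that logistic regression can include ordinal (cumulative) logistic regression, which needs no dichotomy, and that thresholds may be left to the analysis plan or set by the Delphi panel, which section 4.1 has determine outcome measures for difficulty. This stands in part. A reader might infer that these outcomes cannot be modelled at all without an arbitrary split, or that a cut-off will necessarily be chosen after seeing the data. The text supports neither: an ordinal model is possible, and thresholds could still be fixed before analysis. But the article names no ordinal model, and the measures it attaches are binary. This is also not a detail merely left open, because the article itself names the method.

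Other stronger readings also fail:

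- **Clinical grade.** Reducing the CDC/CAMUS grade to complicated/uncomplicated or to major complication/death is an explicit, legitimate choice for a tool that estimates a probability.
- **Section 3.6.** Its wish to separate severe from minor complications concerns the new index formula and sets no requirement for the outcome regressions. The 0 to 100 range there ("which will then be normalised to a value ranging from 0 to 100") belongs to the study's own index; the article does not state the range of the CCI.
- **Size of loss.** The 36% figure is not an estimate for this study. It assumes normality, which CCI and blood loss may not meet, and a median split that the article does not propose.
- **Reach.** The main risk score in section 4.1 is built on major complications or death, where logistic regression is correct.

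**Conclusion.** The point holds in a limited form. The sentence in section 4.1 assigns a model that does not fit three of the four outcomes it names: one primary study outcome and two primary measures of difficulty. With no threshold, no ordinal or continuous-outcome model and only binary performance measures, the plan followed as written depends on an unstated dichotomy of existing data.

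This conclusion rests on the text and needs no distributional assumption. Its size cannot be computed from the article. Under the normal, small-effect assumption the information kept would run from about 64% at a median split to 34% with 10% of patients above the cut. The mortality and major-complication models, and the score derived from them, are unaffected.

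**What to change.** Replace the sentence in section 4.1 so that each outcome has a model suited to its scale:

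- **Mortality and major complication:** binary logistic regression, as now.
- **CCI:** an ordinal cumulative-logit model, or a two-part model if many patients share the lowest value.
- **Blood loss and operating time:** a linear model on the log scale, or a gamma generalised linear model.

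Match the performance measures. For the non-binary outcomes use optimism-corrected R², a rank correlation or ordinal c-index, and calibration plots. Keep Hosmer-Lemeshow and the Brier score for the binary outcomes. If a binary version of CCI, blood loss or operating time is wanted, state and justify its threshold before analysis.

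The cost is a change of wording and slightly more analysis with standard software; no new data are needed. One consequence should be accepted openly: for these three outcomes, the comparison of universal with procedure-specific models can no longer rest on the Brier score and needs its own measure.

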**Table 2 t0010:** Proposed CAMUS intra- and postoperative risk and difficulty estimation indices (IPRADES)

CAMUS IPRADES indices								
Non–organ-specific factors impacting surgical difficulty and risk for complication								
No.	Expected/known (preoperative) parameters				Unexpected/unknown (intraoperative) parameters			
	Parameter	Surgeon		Anaesthetist	Parameter	Surgeon		Anaesthetist
		Surgical difficulty (0 = no, 1 = yes)	Risk for complication (0 = no, 1 = yes)	Risk of complication (0 = no, 1 = yes)		Surgical difficulty (0 = no, 1 = yes)	Risk for complication (0 = no, 1 = yes)	Risk of complication (0 = no, 1 = yes)
1	Diabetes				Intraoperative fluids administered (ml)			
2	ASA classification				Estimated blood loss (ml)			
3	Timing of surgery (AM, PM)				Duration of operation (min)			
4	BMI (kg/m^2^)				ECG abnormalities			
5	Anticoagulant agents				Ventilation difficulties			
6	Elective vs emergency				General overall tissue quality			
7	Previous therapy: non–organ-specific (eg, radiation)				Ooziness/tissue vascularity			
8	Charlson Comorbidity Index				Scarred tissue			
9	Prior abdominal surgical history + type of surgery (eg, bowel resection vs cholecystectomy)				Adherent tissue			
10	Nutrition status (eg, albumin, weight loss, cachexia)				Identifiable planes			
11	Age				Vision			
12	Gender				Vessel injury			
13	Steroid use for chronic condition				Intraoperative blood transfusion			
14	Smoking status				–			
15	Further parameters to be proposed by Delphi experts				Further parameters to be proposed by Delphi experts			
Unexpected/unknown (immediate postoperative) parameters								

Parameter		Surgeon				Anaesthetist		
		Risk for complication (0 = no, 1 = yes)				Risk of complication (0 = no, 1 = yes)		

Acute kidney injury (ie, eGFR decrease by 10 ml/min)								
Significant demand for analgesia (ie, opioids >50 μg)								
Targeted organ-specific factors impacting surgical difficulty and risk for complication (organ-specific scoring system) shown in an exemplary way for laparoscopic/robotic radical prostatectomy								
	Expected/known (preoperative) parameters				Unexpected/unknown (intraoperative) parameters			
	Parameter	Surgeon			Parameter	Surgeon		
		Surgical difficulty (0 = no, 1 = yes)	Risk for complication 0 = no, 1 = yes)			Surgical difficulty (0 = no, 1 = yes)	Risk for complication (0 = no, 1 = yes)	
1	Prostatic size (cc) on MRI (eg, very small or very large)				Narrow bony pelvis			

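### The Comprehensive Complication Index, blood loss and operating time are measured quantities, yet section 4.1 assigns them logistic regression with no outcome cut-off and no model suited to their scale

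*Protocol article*

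**What the plan says.** Section 4.1 (Statistical analysis and development of the score) puts four named outcomes under one method: "Prediction models for mortality, CCI, blood loss, operating time, and other outcomes will be developed using logistic regression". Selection is stepwise by AIC, and C-indices are recorded at each step.

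The standing of these outcomes is set elsewhere in the article:

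- Section 3.7 (Data collection): "The primary study outcomes are the CDC/CAMUS grade or death within 90 d and the Comprehensive Complication Index (CCI".
- Section 4.1, on the difficulty index: "Primary outcome measures for surgical difficulty will include operation duration, blood loss and transfusion, use of haemostatic agents", together with the surgeon's own rating.
- Table 2 lists operation duration in minutes and estimated blood loss in millilitres. Section 3.6 describes the CCI as rising with the number and severity of complications.

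Section 4.1 gives an explicit two-level form to two outcomes only: "using morbidity (complicated/uncomplicated) and mortality (dead/alive) as dichotomous dependent variables, multiple logistic regression models will be derived".

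**The concern.** Ordinary logistic regression needs a yes/no outcome. To fit it to minutes, millilitres or a CCI value, the analyst must first split each outcome at some value, and the article does not give one. Three things follow for these models.

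- They answer a narrower question. They estimate the chance of exceeding the cut and cannot predict minutes, millilitres or a CCI value.
- The predictors that survive stepwise selection, and the C-index at each step, depend on where the cut falls.
- Section 3.7 describes data collection as already done, so a cut fixed later could be fixed with the outcome data in view.

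Splitting a measured outcome also discards information. One of the affected outcomes is primary for the study and two are primary for surgical difficulty.

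**Working it through.** **1. Is there a figure in the plan to reproduce?** Not on this point. The article states no information loss and no outcome cut-off. Its one computed modelling figure, the required sample size of 1180 in section 3.7, does not involve the scale of these outcomes and is not used below.

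**2. Does any other text supply a cut-off or another model?**

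| Place | Content | Does it settle the point? |
|---|---|---|
| Section 3.4 | Blood loss of 100–500 ml is grade 2 | No: it grades blood loss as a risk factor |
| Section 4.1, scoring example | Operation duration banded at 120 and 180 min | No: these are points for a predictor |
| Section 4.1, ordered categories | Refers to the risk score | No: the score is the explanatory variable |
| Section 4.1, hierarchical alternative | Random-intercept models in GLIMMIX | No: no outcome distribution is stated |

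The hierarchical alternative is introduced for the universal and procedure-specific calculators, which are compared on "the c-statistic, the HL statistic (in a revised graphical form), and the Brier score". In their usual form these measure yes/no predictions. The calibration graphs in section 4.1, grouped by equal numbers of events, also presuppose events.

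CCI also abbreviates the Charlson Comorbidity Index in the Introduction. That index is a preoperative predictor in Table 2, so CCI as an outcome can only sensibly mean the Comprehensive Complication Index.

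**3. Information lost by one cut of a normal outcome.** Assumptions, none from the documents: the outcome is normal on a suitable scale (for example log minutes), there is a single cut, and a share p of patients lies above it. The efficiency relative to a linear model is

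E = φ(z)² / [p(1 − p)], where z is the cut in standard units and φ is the normal density.

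- p = 0.50: z = 0, φ = 0.3989; E = 0.1592/0.25 = 0.637; loss 36%
- p = 0.25: E = 0.539; loss 46%
- p = 0.20: E = 0.490; loss 51%
- p = 0.10: z = 1.2816, φ = 0.1755; E = 0.0308/0.09 = 0.342; loss 66%
- p = 0.05: E = 0.224; loss 78%

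**4. Check by simulation.** Setting: 1550 patients (the size of the Bern database in section 3.7), 300 runs, one standard normal predictor with slope 0.15, linear against logistic regression. Loss is 1 minus the squared ratio of the mean test statistics.

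| Outcome shape | Cut at 50th percentile | 75th | 90th |
|---|---|---|---|
| Normal | 39% | 48% | 67% |
| About 40% at a zero floor | 23% | 35% | 58% |

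The first row agrees with the formula to within about 3 percentage points. The second row is nearer to a plausible CCI. The 40% is an assumption, and the comparator is a plain linear model.

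**5. If ordinal logistic regression was meant.** With k equal groups, the loss against using all ranks is about 1/k²: 1/25 = 4% for five groups and 1/9 = 11% for three.

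**The case against.** The strongest reply is that this is a condensed article whose analysis plan is not shown, and that outcome cut-offs are commonly left to that plan. Section 4.1 also leaves the difficulty outcome measures to be settled by Delphi, and section 3.7 says some variables were categorised or transformed. This would answer a complaint about missing detail only. Section 4.1 makes a positive choice of method for named outcomes, and the method does not fit three of them.

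A second reply is that a probability of exceeding a clinically meaningful threshold is useful for stated aims such as critical-care allocation and choice of teaching cases. That stands, provided the threshold is prespecified and justified. It supports a secondary output alongside a model on the measured scale.

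A third is that logistic may have meant ordinal logistic. The loss would then be small, but no ordinal outcome model is named and the performance measures point to yes/no outcomes.

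Some stronger readings are tempting, and the documents do not support them:

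- **The 0–100 difficulty index becomes impossible.** Sections 3.5 and 3.6 build the index from surgeon and anaesthetist weights normalised to 0–100. It does not need predictions in minutes or millilitres.
- **The risk-score weights depend on the cut.** Section 4.1 takes candidates for the risk score from variables that predict major complications or death. The documents do not show a cut of blood loss, time or CCI setting those weights.
- **The 1180 patients shrink to a smaller effective number.** That figure is a required size, already raised by 50% for validation and described as well below what is available. It is not the sample analysed.

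**Conclusion.** The point holds. Section 4.1 assigns logistic regression to one primary outcome and two primary difficulty measures that are measured quantities. It states no outcome cut-off and no alternative suited to their scale. As written, these models cannot be fitted without an unstated choice that shapes their predictors and C-indices.

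The size is conditional. The 36% to 66% range needs a roughly normal outcome and one cut with 50% down to 10% of patients above it. With about 40% zeros the simulated range is 23% to 58% for cuts from the 50th to the 90th percentile. A reader might infer that a third to two thirds of the information is lost for all three outcomes whatever their shape. That does not follow, because the documents give neither the distributions nor the cuts. The mismatch between model and outcome does not depend on these figures.

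**What to change.** Reword the sentence in section 4.1 outcome by outcome:

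- Mortality: logistic regression, as now.
- Operating time and blood loss: a model on their own scale, for example linear regression on the log scale or a gamma model with log link. Any zero values need a stated rule if logs are taken.
- CCI: a proportional-odds model, or a two-part model (any complication, then amount).
- Performance: R-squared or rank correlation plus a calibration slope for these three; C-index, Hosmer-Lemeshow and Brier score for binary outcomes.
- If a threshold probability is wanted for triage or teaching-case selection, prespecify and justify the cut-off and report it as a secondary output.

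The cost is wording and slightly more analysis work, using the same data and standard R functions, with no extra patients. The drawback is that performance measures will differ between outcomes, so the Brier-based comparison of universal and procedure-specific calculators will apply only to the binary ones.

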### Internal validation

4.3

Internal validation of the prediction models will be conducted by randomly splitting the analytic dataset into two subsets: a developmental dataset (two-thirds of the total data) and a validation dataset (one-third of the total data). The C-indices, HL analyses, and Brier scores from the logistic regression analyses will be compared between the developmental model applied to the developmental dataset and the same model applied to the validation dataset.

The use of stepwise, forward-selection logistic regression has faced criticism, particularly in small samples, regarding variable selection and the accuracy of the coefficients and standard errors. However, such criticisms are less relevant when applied to the large sample sizes present in this study. To further test the robustness of the model, bootstrap resampling will be employed for the postoperative mortality model. Full-variable logistic regression models will be performed on each bootstrap sample. The variables will then be ranked by the magnitude of the Wald χ^2^ statistic, and the average rankings from the bootstrap samples will be compared with the order of entry of variables during the forward selection stepwise regression analysis. As such, all steps described above aim to minimise overfitting and improve predictive accuracy.

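### Calibration is judged by the Hosmer-Lemeshow test; regrouping by events does not remove its dependence on sample size, and comparing it between development and validation sets says little

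*Protocol article*

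**What the plan says.** Section 4.1 of the protocol article names the measure: "For model calibration, the Hosmer-Lemeshow (HL) goodness-of-fit test will be used to compare predicted versus observed outcomes between the two cystectomy cohorts". For the morbidity and mortality models it adds that "differences between observed and expected outcomes will be evaluated using the HL test". For universal against procedure-specific models it lists three metrics: "the c-statistic, the HL statistic (in a revised graphical form), and the Brier score".

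The same section recognises a weakness, "Given the HL test’s sensitivity to sample size", and responds that "graphs will be constructed based on sequential groups with equal observed events rather than equal patient numbers". It prefers the Brier score for comparing the universal and procedure-specific calculators. It also plans to compare two years of development data with a third year of validation data.

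Section 4.3 splits the data into "a developmental dataset (two-thirds of the total data) and a validation dataset (one-third of the total data"). It then states: "The C-indices, HL analyses, and Brier scores from the logistic regression analyses will be compared between the developmental model applied to the developmental dataset". The other side of that comparison is the held-out third, scored with the unchanged model.

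The article names no calibration intercept, calibration slope or smoothed calibration curve.

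**The concern.** The HL statistic is a test of exact fit. For a given degree of miscalibration, its excess over the degrees of freedom grows in proportion to the number of patients. Changing how patients are grouped changes where the cut points fall, not this property. So in large pooled cohorts HL will reject models whose miscalibration may be tolerable, and in a small subset it will often pass models whose miscalibration matters.

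The comparison in section 4.3 has a further difficulty. A logistic model fitted by maximum likelihood has calibration slope 1 and intercept 0 in the data it was fitted to. Its HL result there carries almost no information about how well it will be calibrated in new patients. Only the validation third can show that, and there the test is weakest.

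The product is a calculator giving individual risks for counselling, resource allocation and benchmarking. Its users need to know whether the stated risks are too high, too low or too extreme, by how much, and with what uncertainty. An HL statistic or p-value gives none of these.

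**Working it through.** The article states no HL figure, number of groups or event rate, so there is no planned figure to reproduce. The check is by simulation.

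**Inputs from the article.** Bern cystectomy database, n = 1550 (section 3.7), used for illustration. Split 2:1 (section 4.3): 1550 × 2/3 ≈ 1033 and 1550 × 1/3 ≈ 517. Up to 30 predictors (section 3.7).

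**Assumptions.** 10 groups; event rate 25%, with 5% for a rare outcome such as mortality; true calibration slope 0.8; n = 5000 and 10,000 to represent larger pooled cohorts.

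**Step 1: does regrouping remove the dependence on sample size?** A fixed model is applied to new data, with 1000 replicates per cell. HL = Σ (O − E)² / [E(1 − E/n)] over the groups, where n is the group size, referred to chi-square with 10 df at 0.05. Slope 0.8, 25% events:

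| N | Equal-size groups: mean HL, rejection | Equal-event groups: mean HL, rejection |
|---|---|---|
| 517 | 13.8, 19.9% | 13.7, 20.9% |
| 1033 | 16.4, 35.2% | 16.8, 37.2% |
| 1550 | 19.3, 49.8% | 19.5, 51.3% |
| 5000 | 39.4, 98.1% | 39.9, 98.0% |
| 10,000 | 68.3, 100% | 69.4, 100% |

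Miscalibration is identical in every row. For a perfectly calibrated model, rejection at these sizes was 4.6-6.0% with equal-size groups and 4.7-6.3% with equal-event groups.

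The excess of mean HL over its 10 df, divided by N, is nearly constant under equal-event grouping:
- N = 1550: (19.5 − 10)/1550 = 0.0061
- N = 5000: (39.9 − 10)/5000 = 0.0060
- N = 10,000: (69.4 − 10)/10,000 = 0.0059

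So the statistic still scales with N after regrouping.

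An intercept shift of 0.2 logit instead of slope 0.8 gives the same pattern with equal-event groups: 23.0% at 517, 42.6% at 1033, 99.5% at 5000.

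**Step 2: rare outcomes.** At 5% events and slope 0.8, equal-event rejection is 30.2% at N = 517, 23.9% at 1033, 61.5% at 5000 and 94.4% at 10,000. The reversal at the small end reflects inflated type I error: with perfect calibration, equal-event grouping rejects 18.9% at N = 517, against 6.4% with equal-size groups. Cut points set by the outcome would distort the test itself if it were computed on those groups.

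**Step 3: the comparison in section 4.3.** A model is fitted on 1033 patients and applied to 517. With half the predictors null, about 27.5% events, no variable selection, equal-size groups, 8 df in development and 10 in validation (400 replicates):

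| Predictors | Mean HL, development / validation | Rejection, development / validation | Mean validation slope |
|---|---|---|---|
| 10 | 8.0 / 12.3 | 5% / 15% | not reported |
| 20 | 8.0 / 13.6 | 6% / 19% | 0.84 |
| 30 | 8.0 / 17.4 | 5% / 40% | 0.75 |

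With 5 real and 25 noise predictors (500 replicates), rejection was 3.4% in development and 35% in validation, with mean validation slope 0.75. A further run with 30 predictors gave mean HL 8.0 and 16.1, validation rejection of about one third and mean slope 0.74.

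With 30 predictors the overfit is therefore material, the development HL shows nothing, and the validation HL misses it in about 60-67% of splits (100% minus 33-40%).

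**The case against.** The strongest reply is that the plan does not lean on the HL p-value alone. The metric for universal against procedure-specific models is a graphical form of HL, and a grouped observed-against-expected graph does show the size and direction of miscalibration. Section 4.3 speaks of HL analyses, which may include that graph. The Brier score is preferred for comparing calculators. The generic against surgery-specific comparison in section 4.2 uses the same patients, so unequal size does not arise there. No section makes acceptance of a model depend on an HL p-value.

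Most of this stands and limits the point. It does not remove it. The HL test is still the stated calibration measure in section 4.1, and section 4.3 is not restricted to graphs. The graphs give no calibration estimate with a confidence interval, and the Brier score mixes discrimination with calibration.

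It may also be said that slope, intercept and smoothed curves are details for an unseen analysis plan. That would hold if the article were silent. Here it names its calibration measure, admits the weakness and commits to a remedy that does not address it.

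A reader might infer something stronger: that because the validation third is smaller, it will show the smaller HL value and make the model look better calibrated than it did in development. The documents do not support that. Section 4.3 applies a fitted model to its own data and then to new data, so the two sets do not share the same miscalibration. In the simulated split, validation HL exceeded development HL in 70-89% of replicates. The fault in that comparison is low power on one side and calibration by construction on the other.

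**Conclusion.** The point holds as a weakness of method that should be changed. Grouping by equal observed events leaves the HL test dependent on sample size: about 20% rejection at n = 517 and about 98% at n = 5000 for the same slope of 0.8. The comparison between development and validation sets cannot be relied on to reveal overfitting: a mean validation slope near 0.75 is flagged in only about 33-40% of validation sets with N = 1550 and 30 predictors.

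These sizes rest on assumed event rates, predictor effects, 10 groups and assumed degrees of miscalibration, since the article gives none. With fewer predictors or more patients, overfitting is milder: at N = 5000 with 10 to 30 predictors, validation rejection was 9-15% against 3-5% in development. At 25% events, the dependence on N appears under both kinds of miscalibration tried. At 5% events it is clear at N = 5000 and above, but type I error masks it in smaller sets grouped by events.

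**What to change.** In sections 4.1 and 4.3, replace HL-based judgement of calibration with three outputs, reported in the one-third validation set and in the third-year validation data:
- the calibration intercept with its 95% confidence interval (logistic regression of the outcome with the model's linear predictor as offset);
- the calibration slope with its 95% confidence interval (the coefficient of the linear predictor in a logistic regression of the outcome);
- a smoothed calibration curve.

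Drop the HL comparison between development and validation sets. Keep the graph with equal-event groups as display only, and keep the c-statistic and Brier score as planned.

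Bootstrap optimism correction is optional. The bootstrap in section 4.3 only ranks variables for the mortality model, so it would be an additional procedure.

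Cost: apart from that option, a free improvement. It uses the same data and fitted models and needs a few lines of code.
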